| Administration Method of the Study Drugs | Neoadjuvant therapy phase:  Serplulimab: 300 mg, i.v., D1, Q3W;  Thymalfasin: 4.8 mg, subcutaneous injection, twice a week. On Day 1 and Day 4 of each week during Weeks 1–9 or until surgery;  Oxaliplatin: 130 mg/m2, i.v., D1, Q3W;  Tegafur: oral administration: body surface area < 1.25 m^2^, 40 mg each time; body surface area ≥ 1.25 to < 1.5 m^2^, 50 mg each time; body surface area ≥ 1.5 m^2^, 60 mg each time, twice daily for each treatment cycle at D1-D14  After 3 courses of treatment before surgery, radical gastrectomy will be conducted based on evaluation by the investigator within 2–6 weeks after completion of chemotherapy + immunotherapy.  Adjuvant therapy phase: The postoperative treatment of patients will be jointly decided by clinical physicians and patients according to the actual conditions of clinical diagnosis and treatment. |
| **Evaluation Criteria** | Efficacy evaluation:  Evaluation per RECIST v1.1 criteria:   - Pathologic complete response (pCR) rate, defined as the proportion of subjects with no residual viable tumor cells under microscopic examination and negative lymph nodes among the total subjects; - Major pathologic response (MPR) rate, defined as the proportion of subjects with ≤10% viable tumor cells in the resected specimen among the total subjects; - Tumor regression grade (TRG) - Objective response rate (ORR), defined as the proportion of subjects achieving complete response (CR) and partial response (PR) among the total subjects; - Clinical downstaging rate: ypT0 ratio, ypN0 ratio, and preoperative imaging clinical stage will be counted, respectively, to compare with baseline imaging clinical stage downstaging ratio. - Disease-free survival (DFS), defined as the time from surgery to the first radiological disease recurrence or death (whichever occurs first); - Overall survival (OS), defined as the time from enrollment to death of the subject due to any cause;   Safety evaluation:   - Drug-related safety (per CTCAE 5.0): incidence, relationship to study drug and severity of TRAEs, TRAEs ≥ Grade 3, irAEs, etc. - Surgery-related safety (according to Dindo-Demartines-Clavien classification). |

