Through reviewing its mechanism of action, thymalfasin is an immunological peptide with 28 amino acids, which has potential therapeutic effects on patients with various tumors (such as liver cancer, lung cancer, and lymphoma) and diseases (including infectious diseases and chronic hepatitis B), as well as immune improvement effects (*e.g.*, enhancing the response to vaccine) on patients with immunologic inadequacy. It mainly acts on Toll-like receptor 2 (TRL2) and TRL9 on dendritic cells (DCs), and stimulates intracellular signaling pathways including the NF-κB and p38 MAPK pathways, thus increasing the activity of natural killer (NK) cells. Moreover, it promotes the conversion of helper T (Th) cells to Th1 subset, increases the expression of Th1-type cytokines like IL-2 and IFN-γ, elevates the level of cytotoxic T lymphocytes (CTLs), and facilitates DC activation. Tumor cells can be killed through the combined action of NK cells, cluster of differentiation 4 (CD4)^+^ Th1 cells and CTLs. Meanwhile, activated DCs can also generate anti-tumor responses and perform efficient antigen presentation.

Based on the above background and basis, we designed this study to investigate the efficacy and safety of Serplulimab in combination with thymalfasin and SOX regimen for neoadjuvant therapy of locally advanced gastric cancer, and look forward to exploring safer and more effective neoadjuvant regimens for such patients to further benefit patients with gastric cancer.

1. **Objectives and Endpoints**
   1. **Objectives**
2. Primary objective: To investigate the efficacy and safety of Serplulimab in combination with thymalfasin and SOX regimen for neoadjuvant therapy of locally advanced gastric cancer.
3. Secondary objective: To investigate the effect of neoadjuvant therapy with Serplulimab in combination with thymalfasin and SOX regimen on tumor immune micro-environment in locally advanced gastric cancer.
   1. **Endpoints**
      1. **Primary Endpoint**

- Pathological Complete Response (pCR): For patients with surgically resectable gastric cancer after neoadjuvant therapy, the proportion of patients with no residual tumor cells in the primary site to the total enrolled patients.
  - 1. **Secondary Endpoints**
- Major Pathological Response (MPR): For patients with surgically resectable gastric cancer after neoadjuvant therapy, the proportion of patients with less than 10% residual tumor cells in the primary site to the total enrolled patients.

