- Tumor Regression Grade (TRG): It is intended to grade the pathological response of tumor after neoadjuvant therapy and generally divide the grade mainly according to the proportion of fibrosis and residual tumor in the tumor. In this study, Becker criteria are used to grade TGR as follows: TRG1a (no residual tumor), equivalent to pCR; TRG1b (< 10% residual tumor); TRG2 (10% to 50% residual tumor); and TRG3 (> 50% residual tumor). For patients with surgically resectable gastric cancer after neoadjuvant therapy, the proportion of patients with less than 10% residual tumor cells in the primary site to the total enrolled patients (TRG1a & TRG1b).
- Clinical downstaging rate (T and/or N downstaging): ypT0 ratio, ypN0 ratio, and preoperative imaging clinical stage will be counted, respectively, to compare with baseline imaging clinical stage downstaging ratio.
- Objective response rate (ORR): It refers to the proportion of patients whose tumor shrinks to a certain extent and remains for a certain period of time, including CR (Complete Response) and PR (Partial Response) cases. Objective tumor response will be assessed using Response Evaluation Criteria in Solid Tumors (RECIST 1.1 criteria). Patients must have measurable tumor lesions at baseline. Response evaluation criteria are divided into Complete Response (CR), Partial Response (PR), Stable Disease (SD) and Progressive Disease (PD) according to RECIST 1.1 criteria.
- Disease control rate (DCR): It refers to the percentage of confirmed complete response (CR), partial response (PR) and stable disease (SD) cases among evaluable efficacy patients.

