**Study Design Diagram**

**
[figure not shown]
**

1. **Selection Criteria for Subjects**
   1. **Study Population**

cStage III gastric/gastroesophageal junction adenocarcinoma

- 1. **Inclusion Criteria**

1. Male or female patients aged 18–75 years with G/GEJ adenocarcinoma;
2. According to the AJCC 8th edition gastric cancer staging, patients with cStage III (cT_3-4a_N_1-3_M_0_) assessed by abdominal CT and G/GEJ adenocarcinoma diagnosed by gastroscopy and pathology (HER-2 negative or 1+); and patients with gastroesophageal junction (GEJ) cancer will only allow Siewert type III, and Siewert type II subjects who do not require combined thoracotomy to be enrolled.
3. Before enrollment, a doctor in charge of gastrointestinal surgery and an imaging technician jointly assess that the tumor is cStage III and qualified for the study of R0 resection with the purpose of cure, and the patient agrees to receive radical surgery and has no contraindication to surgery as judged by the surgeon;
4. No previous systemic therapy for the current disease, including surgical treatment, anti-tumor chemoradiotherapy/immunotherapy;
5. Expected survival of ≥3 months;
6. There are measurable tumor lesions according to RECIST v1.1 (see Attachment 3 for details);
7. ECOG PS score (see Attachment 4 for details) of 0–1 within 7 days after the first dose;
8. The heart is functioning well and resection for curative purposes can be performed. Patients with underlying ischaemic, valvular or other significant cardiac disease should be evaluated preoperatively by a cardiologist, if clinically indicated;
9. Primary organs are functioning normally and subjects are required to meet the following laboratory parameters:
   1. Absolute neutrophil count (ANC) ≥ 1.5 × 10^9^/L in the absence of granulocyte colony-stimulating factor in the past 14 days;
   2. Platelets ≥ 100 × 10^9^/L without transfusion in the past 14 days;
   3. Hemoglobin > 9 g/dL without or erythropoietin use within the past 14 days;
   4. Total bilirubin ≤ 1.5 × upper limit of normal (ULN); if total bilirubin > 1.5 × ULN but direct bilirubin ≤ ULN, the patient is also allowed to be enrolled;
   5. Aspartate aminotransferase (AST) and alanine aminotransferase (ALT) ≤ 2.5 × ULN
   6. Serum creatinine ≤ 1.5 × ULN and creatinine clearance (calculated using the Cockcroft-Gault formula) ≥ 60 ml/min;
   7. Good coagulation, defined as international normalized ratio (INR) or prothrombin time (PT) ≤ 1.5 times ULN;

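### The primary endpoint pCR is defined both with and without negative lymph nodes, so the same specimens can give two primary results

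*Protocol*

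**What the plan says.** **pCR.** The synopsis (Evaluation Criteria) requires clearance of tumour and nodes: "the proportion of subjects with no residual viable tumor cells under microscopic examination and negative lymph nodes among the total subjects". Section 2.2 (Primary Endpoint) restricts the finding to the stomach: "the proportion of patients with no residual tumor cells in the primary site to the total enrolled patients". The TRG bullet under Secondary Endpoints grades by residual tumour and states "TRG1a (no residual tumor), equivalent to pCR".

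**Nodes elsewhere.** The downstaging bullet in Section 2.2 treats clearance of the primary and of the nodes as separate outcomes: "ypT0 ratio, ypN0 ratio, and preoperative imaging clinical stage will be counted, respectively". Inclusion criterion 2 admits "patients with cStage III (cT_3-4a_N_1-3_M_0_) assessed by abdominal CT".

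**Other mentions.** Sections 6.2, 10 and 12.3 use pCR without defining it. No section ranks the synopsis above the body or the reverse.

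**Major pathologic response (MPR).** The synopsis has "the proportion of subjects with ≤10% viable tumor cells in the resected specimen among the total subjects"; Section 2.2 has "the proportion of patients with less than 10% residual tumor cells in the primary site to the total enrolled patients".

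**The concern.** A definition of the primary endpoint must classify every patient in one way. Here a ypT0N+ patient is a success under one section and a failure under another. If this is left open until the pathology reports are in, the primary rate depends on which page the analyst follows, and that choice could be made with the results in view. The protocol cannot be followed as written for such a patient, because complying with one section breaches the other.

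The population makes the case possible. Every eligible patient is clinically node-positive at entry, so residual nodal disease beneath a cleared primary could occur in any of them.

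**Working it through.** **Step 1. Is it the same definition in shorthand?** No. Section 2.2 names the primary site expressly, while the synopsis adds the nodal condition expressly. The downstaging bullet counts ypT0 and ypN0 separately, so the protocol itself distinguishes the two.

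**Step 2. Classify the possible outcomes.** I read residual tumour cells and residual viable tumour cells as the same thing.

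| Pathology | Synopsis | Section 2.2 and TRG1a |
|---|---|---|
| ypT0, nodes negative | pCR | pCR |
| ypT0, nodes positive | not pCR | pCR |
| residual tumour in primary | not pCR | not pCR |

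Only the middle row differs. Every synopsis responder is also a Section 2.2 responder, so the synopsis rate can never be the higher one.

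**Step 3. Size.** Planned N = 30 (synopsis and Section 3). The protocol gives no null rate, target rate or power, so there is no stated figure to reproduce. If k patients are ypT0N+, then

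difference = k/30.

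- k = 0: 0 points
- k = 1: 1/30 = 3.3 points
- k = 2: 2/30 = 6.7 points
- k = 3: 3/30 = 10.0 points

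The value of k is not in the documents; 0 to 3 is an assumption for illustration.

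**Step 4. Worked illustration.** Suppose 9 of 30 patients are ypT0. Intervals are exact (Clopper-Pearson) 95%.

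| Definition | ypT0N+ among the 9 | Rate | 95% CI |
|---|---|---|---|
| Section 2.2 | any | 9/30 = 30.0% | 14.7 to 49.4 |
| Synopsis | 0 | 9/30 = 30.0% | 14.7 to 49.4 |
| Synopsis | 1 | 8/30 = 26.7% | 12.3 to 45.9 |
| Synopsis | 2 | 7/30 = 23.3% | 9.9 to 42.3 |
| Synopsis | 3 | 6/30 = 20.0% | 7.7 to 38.6 |

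**Step 5. Denominator.** The synopsis divides by total subjects and Section 2.2 by total enrolled patients; these read alike. Section 12.1, however, builds the full analysis set (FAS) on the intention-to-treat principle, names that as the primary population, and limits it to patients who received Serplulimab and had one efficacy evaluation. An enrolled patient without either is in the Section 2.2 denominator but not in the FAS.

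**Step 6. MPR.** The cut-off differs at exactly 10%, and so does the tissue assessed (whole resected specimen against primary site). The protocol's own grading puts under 10% in TRG1b and 10% to 50% in TRG2. A specimen read as exactly 10% is therefore MPR in the synopsis, but TRG2 and not MPR in Section 2.2.

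**The case against.** The strongest reply is that the conflict may never matter. If no resected patient is ypT0N+, both definitions give the same number, and the documents offer no frequency for that finding. The cN1-3 requirement is a CT assessment, not pathological proof of nodal disease. This stands: it supports saying that two results are possible and no more. It does not remove the contradiction, since k is unknown until the pathology is read.

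A second reply is that a statistical analysis plan could settle the matter. It could choose one version, but it would then contradict another part of the protocol. The fault is two statements that conflict, not something left unsaid.

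A reader might also infer that one patient could change the conclusion against the background pCR rate of about 20% in Section 1. At 11/30 = 36.7% the exact interval (19.9 to 56.1) includes 20%; at 12/30 = 40.0% (22.7 to 59.4) it does not. The documents do not support that reading. They plan no test against 20%, they describe the analysis as mainly descriptive, and they do not say which pCR definition the background figure uses. Nor is the flip robust: at 11/30 the Wilson interval is 21.9 to 54.5, and the exact two-sided binomial p-value against 20% is 0.036.

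Finally, a reader might take the synopsis as correct and Section 2.2 as inflating the result. Nothing in the protocol establishes this. The Section 2.2 texts speak of the primary site, or of residual tumour without mention of nodes, and the synopsis is the one that differs. All that follows is that the synopsis version is stricter.

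**Conclusion.** The point holds and concerns the primary endpoint. The two definitions of pCR differ by exactly the number of ypT0N+ patients, at 3.3 points each with N = 30, and the protocol does not say which applies. The range of 0 to 10 points rests on an assumed 0 to 3 such patients; it is an illustration, not a forecast. The risk comes from the two definitions themselves: in a single-arm trial there is no between-group comparison for the open label to bias. The denominator mismatch with the FAS belongs to the same repair. The MPR conflict is real but secondary.

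**What to change.** Before any pathology is read:

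- Choose one pCR definition with the nodal condition explicit, and use it word for word in the synopsis, Section 2.2 and the TRG text. ypT0N0 is the stricter option and cannot give the higher rate, but the choice is the sponsor's to make and justify.
- Report the other measure (for example ypT0 with any nodal status, or TRG1a) under its own name. If negative nodes are required, remove the statement that TRG1a is equivalent to pCR.
- State the pCR denominator so that it agrees with the primary analysis population, reconciling total enrolled in Section 2.2 with the FAS in Section 12.1.
- Give MPR one cut-off and one tissue basis throughout. Under 10% matches the protocol's own grouping of TRG1a with TRG1b.

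The cost is protocol wording. N does not change, and the planned ypN0 ratio already requires nodal pathology. The downside of keeping the stricter version is that the reported pCR may be lower, by 3.3 points for each ypT0N+ patient with 30 in the denominator.

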| **Study Design** | This is a prospective, single-center, single-arm, phase II clinical study. This study plans to enroll 30 treatment-naïve and operable patients with locally advanced adenocarcinoma gastric. After signing the informed consent form, patients will be screened to ensure they meet the inclusion and exclusion criteria. Before surgery, patients will receive three cycles of neoadjuvant therapy with Serplulimab combined with the SOX regimen and nine weeks of thymalfasin. The efficacy of neoadjuvant therapy and the feasibility of radical D2 resection will be assessed via imaging after Cycle 2 and Cycle 3. Radical gastrectomy will be performed within 2–6 weeks after completing the third dose. The postoperative treatment of patients will be jointly decided by clinical physicians and patients according to the actual conditions of clinical diagnosis and treatment.  The main observation indicator is the pCR rate after neoadjuvant therapy;  Safety assessment: The safety will be assessed once after each cycle of neoadjuvant therapy and at 30 days after surgery;  Event follow-up: The events will be followed up every 3 months during the first year after surgery, and once every 6 months from the first to the second years, until the second year. |

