**After enrollment**:

1. Endoscopically, tumor tissue will be collected from patients for subsequent immunofluorescence assay.
2. Patients should complete hematology, blood biochemistry, urinalysis, coagulation function, tumor markers, thyroid function, cardiac function markers, pre-transfusion eight-item panel, and other blood tests within 7 days (≤7 days) before the first neoadjuvant therapy, and complete ECOG scoring (0–1 points). After evaluation, patients should have no significant contraindications to immunotherapy or chemotherapy, and are eligible for neoadjuvant immunotherapy combined with thymalfasin and chemotherapy (regardless of PD-L1 expression, MMR, or MSI status).
   1. **Neoadjuvant Therapy Period**
3. Adverse reactions after treatment should be assessed within 14 days from the end of each cycle of neoadjuvant therapy to the start of the next cycle, including symptom-directed physical examination, 12-lead electrocardiogram, and ECOG score.
4. Blood tests including hematology, blood biochemistry, urinalysis, coagulation function, tumor markers, thyroid function, and cardiac markers should be completed within 3 days (≤3 days) prior to the second neoadjuvant therapy.
5. A non-contrast chest CT scan and an abdominal contrast-enhanced CT should be performed to evaluate ORR and DCR and adverse reactions of patients should also be assessed within 7 days (≤7 days) before the start of Cycle 3 of neoadjuvant therapy.
6. Blood tests including hematology, blood biochemistry, urinalysis, coagulation function, tumor markers, thyroid function, and cardiac markers should be completed within 3 days (≤3 days) prior to the third neoadjuvant therapy;
7. Abdominal contrast-enhanced CT and non-contrast + contrast-enhanced gastric tumor MRI should be performed within 7 days after completion of neoadjuvant therapy (after Cycle 3) to assess the feasibility of surgery, ORR, and DCR. Blood tests including hematology, blood biochemistry, urinalysis, coagulation function, tumor markers, thyroid function, and cardiac markers, as well as electrocardiogram (ECG) and ECOG scoring should be completed within 7 days (≤7 days) before surgery.

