Per-protocol Set (PPS): Including all patients that comply with the study protocol, have good compliance, do not take prohibited medications during the study, and complete the required content in the case report forms. No imputation will be made for missing data. Statistical analyses of the drug's efficacy will be performed based on both the FAS and PPS.

Safety Analysis Set: Including all enrolled patients who have received at least one complete cycle of neoadjuvant immunotherapy plus chemotherapy and have safety records after using Serplulimab. This data set is used for safety analysis.

- 1. **Statistical Analysis Plan**

The results of this study will be primarily analyzed using statistical descriptive methods. For measurement data, the mean, standard deviation, median, max, and min values will be listed. For enumeration data and ranked data, the frequency (constituent ratio), rate, and CIs will be listed.

All statistical analyses will be programmed and calculated using SAS 9.2 Statistical Analysis Software. All statistical tests will be performed using two-sided tests, where P < 0.05 will be considered statistically significant for the tested differences, and CIs will be presented as 95% CIs.

- 1. **Efficacy Analysis**

The primary efficacy endpoint is the pCR rate. The ORR and its 95% CI will be calculated by the best overall response (BOR).

The Kaplan-Meier method will be used to plot the DFS curve and estimate the median DFS with its 95% CI, as well as the OS curve and its 95% CI.

Statistical analysis will be performed using SAS 9.4 software, where P < 0.05 will be considered statistically significant for the tested difference.

- 1. **Drug Safety Evaluation**

The AEs and adverse reactions that occurred in this study will be primarily described by descriptive statistical analysis, with a listing provided (adverse reactions are defined as “AEs with a ‘definitely related/probably related/possibly related’ relationship to the study drug”). The laboratory test results describe the conditions where values are normal before treatment but become abnormal afterward, along with the relationship with the study drug in case of abnormal changes. Chi-square test will be performed for the incidence of related adverse reactions between different stratified groups.

1. **Quality Control and Quality Assurance**

The study personnel must be physicians trained in clinical trials and work under the supervision of senior professionals.

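### ORR and DCR are read from the same two preoperative scans under different denominators and response rules, so DCR is raised and need not equal ORR plus stable disease

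*Protocol*

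**What the plan says.** The Protocol Synopsis (Evaluation Criteria) defines ORR as "the proportion of subjects achieving complete response (CR) and partial response (PR) among the total subjects". Section 2.2 (Secondary Endpoints) describes it as "the proportion of patients whose tumor shrinks to a certain extent and remains for a certain period of time", gives no length for that period, and then refers to RECIST 1.1 for the assessment. Section 12.3 calculates ORR and its confidence interval from best overall response.

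DCR is defined only in section 2.2: "It refers to the percentage of confirmed complete response (CR), partial response (PR) and stable disease (SD) cases among evaluable efficacy patients". The text does not say what makes a case confirmed or a patient evaluable.

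Both rates come from the same imaging. Section 6.2 assigns to ORR and DCR a CT in the week before Cycle 3 and a second examination to be "performed within 7 days after completion of neoadjuvant therapy (after Cycle 3) to assess the feasibility of surgery, ORR, and DCR". Note 16 of the Study Flow Chart places the next scheduled imaging after surgery. It also lets the investigator add tumour assessments when clinically needed.

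Section 12.1 brings in a third population. The full analysis set (FAS) requires a patient to have received Serplulimab and to have one efficacy evaluation, and the same paragraph names ITT as the primary population.

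**The concern.** Every responder is also a patient with disease control, so on one set of patients DCR should be ORR plus the stable-disease rate. The definitions do not secure this. A patient who never has a post-baseline scan, for example after an early withdrawal or death, stays in the ORR denominator as a non-responder but drops out of the DCR denominator. Such patients are more likely to be failures than successes, so leaving them out makes DCR look better.

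The response rules also pull apart. Best overall response credits a partial response (PR) seen once. The persistence clause for ORR and the word *confirmed* for DCR both ask for a later observation, and for a response first seen after Cycle 3 no such observation is scheduled before the tumour is removed. In an open-label, single-arm trial of 30 patients, whoever reports these rates would have to choose among the readings, possibly after seeing the data.

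**Working it through.** The Protocol gives no figure for ORR or DCR, so there is nothing to reproduce. The check has four parts.

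**1. The rules side by side**

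| Source | Response rule | Denominator |
|---|---|---|
| ORR, Synopsis | CR or PR | all subjects |
| ORR, section 2.2 | CR or PR by RECIST 1.1; shrinkage lasting an unstated time | patients, not specified further |
| ORR, section 12.3 | best overall response | not stated |
| DCR, section 2.2 | confirmed CR, PR or SD | evaluable patients, not defined |
| FAS, section 12.1 | not applicable | received Serplulimab and has one efficacy evaluation |

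The Synopsis and section 12.3 fit together: one gives the categories and denominator, the other the per-patient rule. The conflict lies between these two and section 2.2.

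**2. Denominator effect**

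Let N be all subjects, m those without a post-baseline scan, R the responders and S the patients with stable disease as best response. As defined, ORR = R/N and DCR = (R + S)/(N − m). Nested rates would need DCR = (R + S)/N. The defined DCR is therefore larger by the factor N/(N − m).

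N = 30 is the Protocol's planned enrolment. The other counts are assumptions for illustration: R = 18, S = 8, 1 progression, m = 3. All 18 responses are counted as controlled, so only the denominator is at work.

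- ORR = 18/30 = 60.0%
- Stable disease = 8/30 = 26.7%
- ORR plus stable disease = 26/30 = 86.7%
- DCR as defined = 26/27 = 96.3%
- Gap = 96.3 − 86.7 = 9.6 percentage points

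With 26 controlled cases held fixed and m = 0, 1, 2, 3 or 4, the defined DCR is 26/30 = 86.7%, 26/29 = 89.7%, 26/28 = 92.9%, 26/27 = 96.3% or 26/26 = 100.0%.

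**3. If the FAS set both denominators**

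On the same counts, and if the unscanned patients have no other efficacy evaluation, ORR = 18/27 = 66.7% and DCR = 26/27 = 96.3%. The rates then nest, since 18/27 + 8/27 = 26/27, but both exceed the all-subject values of 60.0% and 86.7%.

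**4. Room for confirmation before surgery**

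Count days from Cycle 1 Day 1 as day 0, with 21-day cycles and visit windows ignored. The third dose falls on day 42 and Cycle 3 ends on day 63. Scan 1 falls on days 35–42. Scan 2, timed from the end of Cycle 3 as in section 10, falls on days 63–70. No confirmation interval is stated; 28 days is assumed here.

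- Surgery 2–6 weeks after the third dose (Synopsis Study Design, section 3): days 56–84. The longest gap from scan 2 is 84 − 63 = 21 days. The earliest 28-day confirmation is day 91, which is too late.
- Surgery 2–6 weeks after completion of treatment (sections 6.2 and 10), read as the end of Cycle 3: days 77–105. The longest gap is 105 − 63 = 42 days, and day 91 fits.
- If completion means the third infusion, scan 2 falls on days 42–49 and confirmation on days 70–77, inside days 56–84.
- If completion means the last Tegafur dose (about day 56), scan 2 falls on days 56–63 and confirmation on days 84–91. This just reaches day 84 with surgery counted from the third dose, and falls inside days 70–98 counted from completion.

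A 28-day confirmation is thus ruled out under only one combination of readings. Under all the others it would still need a scan that is not on the schedule.

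**The case against.** The strongest objection is the FAS. Section 12.1 requires one efficacy evaluation and efficacy is analysed in the FAS and the per-protocol set, so a patient with no scan may leave both rates and the denominators may nearly coincide. That is a fair reading. But nothing equates either all subjects or evaluable patients with the FAS, the same paragraph calls ITT primary, and this reading cures the mismatch only by raising both rates.

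A reader might infer that a response first seen after Cycle 3 can never be confirmed. The Protocol does not support that: it states no interval, allows extra scans, and counts the surgery window from different points. Only the absence of a scheduled scan is established.

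A reader might also infer that a PR before Cycle 3 followed by progression fails the section 2.2 definition of ORR. With no period stated, this cannot be shown. Likewise, missing confirmation leaves DCR unchanged if an unconfirmed PR still counts as stable disease; the Protocol does not say whether it does.

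Definitions of evaluable and confirmed could be left to an analysis plan. What the Protocol itself fixes in conflicting terms is a different matter. Finally, section 10 makes imaging response supplementary to pathology, and no hypothesis is tested on ORR or DCR. That limits the weight of the point but does not remove it.

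**Conclusion.** The point holds as a minor inconsistency between secondary endpoints. Under the stated denominators, unscanned patients count against ORR and vanish from DCR, which raises DCR and breaks its link to ORR. In the illustration the rise is 9.6 points with 3 of 30 patients unscanned; it is zero if every patient is scanned. Those counts are assumed, not taken from the Protocol.

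The effect of the persistence and confirmation wording cannot be sized, because no period is given and the number of late responses is unknown. Over 30 subjects, each response accepted under one reading and rejected under another moves ORR by 1/30 = 3.3 points.

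It would be wrong to conclude that the trial's main result is at risk. The pathologic complete response rate does not depend on these scan rules.

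**What to change.** Define both endpoints by one rule: RECIST 1.1 best overall response over the preoperative scans, confirmation not required, in all enrolled patients. A patient with no post-baseline scan counts as a non-responder for ORR and as not controlled for DCR. This agrees with the Synopsis and section 12.3, and with the denominator of all enrolled patients that section 2.2 already uses for pathologic complete and major response.

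In section 2.2, delete the word *confirmed* and the restriction to evaluable patients from the DCR definition, and delete the persistence clause from the ORR definition. In section 12.1, state that the FAS requirement of one efficacy evaluation does not set the ORR or DCR denominator.

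The cost is wording only, with no added scans. DCR becomes slightly less favourable, and responses must be labelled unconfirmed in the report. The differing starting points of the surgery window should be reconciled by the sponsor as a separate matter; this change does not depend on which one is kept.
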